### Study design

This is a multi-center, two-group, parallel, RCT to compare the effects of two 12-week interventions: Internet-based Cognitive Behavioral Treatment (iCBT) plus treatment as usual (TAU) or TAU only, designed to demonstrate statistical superiority. The proposed flow of participants through the trial is shown in Fig. 2. Assessments and biomarkers are completed by all participants at baseline (pre randomization) and post treatment at week 13 and week 52.

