#### Randomization, treatment allocation and blinding

The randomization was done in blocks of 20 according to a fully automated and concealed procedure in the online platform that was programmed in the content management system Drupal (drupal.org) by the fourth author. The research nurse randomizes all eligible participants via the online platform by activating a link that only she has access to. Type of treatment (iCBT + TAU vs TAU) is not blinded neither for the participants nor the research nurse. Hence, unblinding of participants and the research nurse will not be necessary during the trial. Responsible researchers as well as data analysts will not have access to the codes concerning which experimental condition the participants participate in until after completion of analysis of the primary outcome measure. Hence, the risk of bias in the interpretation of the study’s result is minimal.

The participants are informed by the research nurse about their group allocation and are scheduled for a blood test for biomarkers and an appointment with the GP at the PC clinic, ideally within 2–3 weeks. The GPs give all participants feedback on the assessment and biomarkers and design a treatment plan based on current routines at the PC clinic. For those randomized to iCBT, the Internet program will be made available the following Monday after randomization.

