#### Outcome measures

Primary outcome is change in alcohol consumption in mean grams per week and mean number of days with heavy drinking (that is > 4/5 drinks for women and men) the last 30 days from baseline to 12 and 52 weeks post inclusion. A drink contains 12 g of alcohol.

For all secondary outcomes mean change from baseline to 12 and 52 weeks post inclusion applies; hazardous drinking and severity of dependence, health-related quality of life, symptoms of depression and anxiety and difference in biomarker levels of heavy drinking and liver pathology.

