#### Baseline and follow-up assessments

Questionnaires: Time Line Follow Back 30 days [﻿20﻿] is used to assess mean weekly alcohol consumption and heavy-drinking days. Severity of hazardous drinking and dependence is assessed with the Alcohol Use Disorders Identification Test (AUDIT) [22] and the *ICD-10* criteria for alcohol dependence (The World Health Organization, 1992). Symptoms of anxiety and depression are assessed with the Hospital Anxiety and Depression Scale (HADS) [22]. The EuroQol five dimensions, five levels health survey (EQ-5D-5 L) questionnaire measure health-related quality of life [23]. Satisfaction with treatment is assessed, only at 12 weeks’ follow up, with the Client Satisfaction Questionnaire (CSQ) [24].

Biomarkers: blood is analyzed for standard biomarkers of heavy drinking and liver pathology at each assessment; levels of phosphatidylethanol (PEth); gamma-glutamyl transferase (GGT); aspartate amino transferase (AST) and alanine amino transferase (ALT).

Biological specimens will not be stored as a part of the study. Results from blood samples are provided via the patient file system at the PC clinics and blood samples are destroyed after analysis.

Patients will be contacted by automatically created messages in the web-based treatment platform and by the research nurse when necessary during weeks 13 and 52 in order to conduct the follow-up assessments and blood tests. At week 13 the Client Satisfaction Questionnaire (CSQ) is added. Assessment completeness is checked automatically on the treatment platform and if not completed participants cannot proceed to the next step. Participants will be contacted by the research nurse and reminded if assessments are not completed using a combination of messages from the treatment platform, phone calls, emails and text messaging in order to improve retention in treatment and prevent loss to follow-up over the follow-up period. The research nurse will also remind the participants to leave the blood tests during weeks 13 and 52 and collect the results from the patient files.

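### The protocol contradicts itself on whether the baseline biomarker sample is taken before or after randomisation, so change from baseline in PEth, GGT, AST and ALT may be biased

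*Protocol article*

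**What the plan says.** All references are to the protocol article.

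- **Study design** gives the timing as: "Assessments and biomarkers are completed by all participants at baseline (pre randomization) and post treatment at week 13 and week 52".
- **Screening and baseline assessment** describes what happens before randomisation: web-based screening, web-based baseline assessment, and a telephone call with the research nurse. No blood test is mentioned.
- **Randomization, treatment allocation and blinding** gives the next steps. The nurse randomises by activating a link, and then: "The participants are informed by the research nurse about their group allocation and are scheduled for a blood test for biomarkers". The same sentence goes on to name a GP visit and a target delay: "and an appointment with the GP at the PC clinic, ideally within 2–3 weeks". In the iCBT arm, "the Internet program will be made available the following Monday after randomization". At the visit, "The GPs give all participants feedback on the assessment and biomarkers". Neither participants nor nurse are blinded.
- **Baseline and follow-up assessments** says that "blood is analyzed for standard biomarkers of heavy drinking and liver pathology at each assessment" and names PEth, GGT, AST and ALT.
- **Outcome measures** lists "difference in biomarker levels of heavy drinking and liver pathology" among the secondary outcomes, all of which are defined as mean change from baseline.

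**The concern.** A change score, or a mixed model that takes the first value as time zero, compares the arms fairly only if that value cannot have been influenced by allocation. The procedure as written does not secure this, in two ways.

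1. If blood is drawn after iCBT has opened, any early effect of iCBT is already in the first value, in one arm only. Subtracting it removes part of the effect being estimated.
2. Even if blood is drawn before iCBT opens, participants already know their arm. Whether they attend for the test, and how much they drink before it, may depend on that knowledge.

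The four biomarkers are the only outcomes listed that do not rest on reports by unblinded participants, so their between-arm contrast should be clean. There is also a reporting risk: a value taken after randomisation could be published as a pre-randomisation baseline. The planned tests of baseline group differences could then show an early treatment effect as if it were chance imbalance.

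**Working it through.** **Step 1. Is the post-allocation draw the baseline sample?**

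Blood is analysed at every assessment, and there are three: baseline, week 13 and week 52. The draw arranged when allocation is disclosed precedes the GP's feedback on biomarkers and the treatment plan, so it is not a follow-up sample. No earlier draw appears in the text. It is therefore the baseline sample, and the Study design statement and the procedure cannot both be right.

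**Step 2. How much iCBT access could precede it?**

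The Monday following randomisation is 1 day away (randomised on a Sunday) to 7 days away (randomised on a Monday).

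Access before the draw = days from randomisation to draw − days from randomisation to that Monday.

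| Draw, days after randomisation | iCBT access before the draw |
|---|---|
| before that Monday | 0 days |
| 7 | 7 − 7 = 0 to 7 − 1 = 6 days |
| 14 | 14 − 7 = 7 to 14 − 1 = 13 days |
| 21 | 21 − 7 = 14 to 21 − 1 = 20 days |

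The 14- and 21-day rows apply the protocol's 2 to 3 weeks to the blood test. The sentence may mean only the GP visit.

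**Step 3. What would this do to change from baseline?**

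Let δ be the true between-arm difference at follow-up, and f the share of it already present at the first draw.

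- Contrast in change = δ − fδ = (1 − f)δ.
- If the first value is instead a covariate with slope β, the contrast is (1 − βf)δ, so the loss is smaller. The protocol does not name its baseline covariates, so this case is conditional.

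The documents do not give f. Purely as an illustration, assume the effect builds linearly over the 12-week intervention (84 days), so f = days of access / 84:

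- 7 days: 7/84 = 8.3%
- 13 days: 13/84 = 15.5%
- 14 days: 14/84 = 16.7%
- 20 days: 20/84 = 23.8%
- draw before access: 0%

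A draw at 14 to 21 days thus attenuates the change contrast by about 8% to 24%. With an assumed β of 0.3 to 0.7, the covariate version loses 0.3 × 8.3% = 2.5% to 0.7 × 23.8% = 16.7%. These shares refer to the end-of-treatment contrast. For week 52 they hold only if the effect stays at its 12-week level.

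**Step 4. Is there a plan figure to reproduce?**

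There is none for biomarkers. The only sample-size figure is 100 per arm for a standardised effect of 0.4, two-sided 0.05 and 80% power. It reproduces: 99 per arm by the normal approximation, and 80.4% power at 100 per arm by the t test. It was not set for PEth or liver enzymes, and nothing above depends on it.

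**The case against.** The strongest reply is that this is a contradiction in the text, not a demonstrated bias. The Study design section says plainly that sampling precedes randomisation, and the SPIRIT and participant-flow figures, which might settle the matter, are not available here. The 2 to 3 weeks may govern only the GP appointment; since the GP feeds back the biomarker results, blood must be drawn earlier and might be drawn before iCBT opens. An early iCBT effect is assumed. Allocation-dependent attendance could push the contrast either way. Only secondary outcomes are involved, and attenuation would be conservative.

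Most of this stands and limits the conclusion, but it does not remove the point. The detailed procedure has randomisation and disclosure before the blood test, and no visible text reconciles that with the Study design section. A draw before the first Monday would avoid iCBT exposure but would still follow open-label disclosure.

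A reader might infer three stronger things that the documents do not support:

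- **That the biomarker baseline is certainly contaminated.** The documents show that it may be; actual draw dates are not given.
- **That biomarker power falls by a stated amount.** The effect of 0.4 and the 80% power come from a calculation not made for biomarkers, and a very large f, such as half the effect, has no basis in the text.
- **That the primary result is compromised.** Grams per week and heavy-drinking days come from the Time Line Follow Back questionnaire, part of the web baseline assessment completed before randomisation.

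**Conclusion.** The protocol contradicts itself on the timing of the baseline biomarker sample, and that much is certain from the text. If the procedure was followed as written, the first sample comes after randomisation and disclosure of allocation, and possibly after iCBT access has opened. Change from baseline in the four biomarkers may then be biased: toward no difference if iCBT acts early, and in either direction if attendance or drinking before the test depends on known allocation.

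The size cannot be derived from the documents. The range of about 8% to 24% rests on two assumptions, a draw at 14 to 21 days and a linear build-up of effect; with a draw before access, attenuation from iCBT exposure is 0%. The point concerns secondary outcomes only. A comparison of week-13 and week-52 levels that does not use the first sample is free of this problem.

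**What to change.** 1. Reconcile Study design with the randomisation section. If the first sample is not taken before randomisation, correct the Study design statement.
2. For every participant whose first sample follows randomisation, do not treat it as a baseline, whether as a subtracted value, as time zero in a mixed model or as a covariate. Compare week-13 and week-52 biomarker levels between arms, adjusted for pre-randomisation Time Line Follow Back grams per week and AUDIT score.
3. Report the interval from randomisation to first sample by arm, so that readers can judge possible exposure.

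The cost is a text correction, a changed analysis sentence and retrieval of sample dates; no extra blood is needed. Some precision is lost, because the first biomarker value would probably predict follow-up levels better than the questionnaire measures do.

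Drawing blood before randomisation for remaining recruits is optional. The protocol is dated 5 June 2019 and recruitment runs from September 2017 to December 2019, so about 21 of some 27 months had passed, and the change would add a clinic step to a web and telephone process. If it is made, the follow-up-level analysis in item 2 should still be used for all participants, so that two definitions of baseline are not mixed in one trial.

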#### Treatment as usual (TAU)

The GPs design a treatment plan based on current routines for treating alcohol problems at the PC clinic. The fact that all participants are offered contact with a GP enables participants in need of specialized care of any kind to be referred by the GP. All GPs are offered a brief training in giving feedback on the assessment and biomarkers and the use of medication for treatment of alcohol dependence. Together this serves as the base of TAU which is provided to the participants in both study arms.

#### Internet-based Cognitive Behavioral Therapy

The intervention group will be given iCBT in addition to TAU. The iCBT program is based on the self-help material used in previous studies on the Internet [18, 21] and in primary care [13]. iCBT includes five elements: (1) Motivation to cut down or stop drinking, (2) Goal-setting for alcohol consumption per occasion and weekly consumption and self-control strategies; for example, not to have alcohol at home and strategies to drink more slowly, (3) Chart risk situations and conduct behavior analysis on occasions with too much alcohol, (4) Plan alternative activities to drinking alcohol and (5) Relapse prevention and crisis plan and mapping of life situations or stressors that can lead to relapse. The intervention is open-ended, meaning that participants can log on as often and for as long as they want.

For each assignment an informational text is provided and a home assignment is included. iCBT is an extended self-help intervention with automated feedback where participants repeatedly are reminded to start and complete every assignment.

#### Outcome measures

Primary outcome is change in alcohol consumption in mean grams per week and mean number of days with heavy drinking (that is > 4/5 drinks for women and men) the last 30 days from baseline to 12 and 52 weeks post inclusion. A drink contains 12 g of alcohol.

For all secondary outcomes mean change from baseline to 12 and 52 weeks post inclusion applies; hazardous drinking and severity of dependence, health-related quality of life, symptoms of depression and anxiety and difference in biomarker levels of heavy drinking and liver pathology.

#### Baseline and follow-up assessments

Questionnaires: Time Line Follow Back 30 days [﻿20﻿] is used to assess mean weekly alcohol consumption and heavy-drinking days. Severity of hazardous drinking and dependence is assessed with the Alcohol Use Disorders Identification Test (AUDIT) [22] and the *ICD-10* criteria for alcohol dependence (The World Health Organization, 1992). Symptoms of anxiety and depression are assessed with the Hospital Anxiety and Depression Scale (HADS) [22]. The EuroQol five dimensions, five levels health survey (EQ-5D-5 L) questionnaire measure health-related quality of life [23]. Satisfaction with treatment is assessed, only at 12 weeks’ follow up, with the Client Satisfaction Questionnaire (CSQ) [24].

Biomarkers: blood is analyzed for standard biomarkers of heavy drinking and liver pathology at each assessment; levels of phosphatidylethanol (PEth); gamma-glutamyl transferase (GGT); aspartate amino transferase (AST) and alanine amino transferase (ALT).

Biological specimens will not be stored as a part of the study. Results from blood samples are provided via the patient file system at the PC clinics and blood samples are destroyed after analysis.

Patients will be contacted by automatically created messages in the web-based treatment platform and by the research nurse when necessary during weeks 13 and 52 in order to conduct the follow-up assessments and blood tests. At week 13 the Client Satisfaction Questionnaire (CSQ) is added. Assessment completeness is checked automatically on the treatment platform and if not completed participants cannot proceed to the next step. Participants will be contacted by the research nurse and reminded if assessments are not completed using a combination of messages from the treatment platform, phone calls, emails and text messaging in order to improve retention in treatment and prevent loss to follow-up over the follow-up period. The research nurse will also remind the participants to leave the blood tests during weeks 13 and 52 and collect the results from the patient files.

If considerable somatic or psychiatric complications occur during the study, the research personnel or the GPs can take the initiative to withdraw the patient from the study and if applicable make a referral to an appropriate care-giver. Following completion of the study no post-trial care is planned as part of the study, but since all patients are in contact with their GPs further treatment may be provided within the framework of TAU.

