### Statistical analyses and sample size calculations

Baseline participant characteristics stratified by treatment group will be presented. Group differences will be tested using a *t* test for continuous variables and chi-square tests for categorical outcomes. Multiple imputation will be used to replace missing internal values where appropriate. Within-group changes in the primary outcome (alcohol consumption) and secondary outcomes (*ICD-10* criteria, AUDIT scores, depression, anxiety, EQ-5D-5 L and biomarkers) at 12 and 52 weeks will be analyzed according to the intention-to-treat principle, using linear mixed models and Poisson regression where appropriate. The models will further be adjusted for baseline covariates and treatment adherence. Per-protocol analyses will also be presented. All tests will be two-sided and *p* values of less than 0.05 considered statistically significant.

The study is designed to demonstrate statistical superiority. An effect-size of 0.61 has been shown in previous Internet studies on high consumers in the general population [25]. Due to a lack of studies on alcohol-dependent patients, our estimate is based on a more conservative effect-size of 0.4, which requires the estimated sample size of 100 participants in each arm to get a power of 80% and a statistically significance 0.05 when using a *t* test. Given an estimated dropout in iCBT of 30%, 260 participants are included in the study [26].

No interim analyses are planned.

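### Staff-initiated withdrawal is written as leaving the study, without saying that outcome collection continues, so outcome-related data may be missing from the intention-to-treat analysis

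*Protocol article*

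**What the plan says.** The withdrawal rule is in the Protocol article under *Baseline and follow-up assessments*. Its trigger reads "If considerable somatic or psychiatric complications occur during the study", and in that case "the research personnel or the GPs can take the initiative to withdraw the patient from the study", with a referral where one applies. No threshold is given for the trigger. The rule names the study, not the treatment, as what the patient leaves, and it does not say whether assessments go on afterwards.

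Four other places bear on it:

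- *Treatment as usual (TAU)*: contact with a GP, offered in both arms, "enables participants in need of specialized care of any kind to be referred by the GP". Referral is therefore also part of ordinary care within the trial.
- *Randomization, treatment allocation and blinding*: the type of treatment "is not blinded neither for the participants nor the research nurse". By contrast, "Responsible researchers as well as data analysts will not have access to the codes" until the primary outcome has been analysed. GPs are not mentioned.
- *Outcome measures*: the secondary outcomes include "symptoms of depression and anxiety and difference in biomarker levels of heavy drinking and liver pathology".
- *Statistical analyses and sample size calculations*: changes at 12 and 52 weeks "will be analyzed according to the intention-to-treat principle, using linear mixed models and Poisson regression where appropriate". Multiple imputation is foreseen for missing values described as internal. Participants withdrawn by staff are not mentioned.

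**The concern.** An intention-to-treat comparison is at its strongest when outcomes are sought from everyone randomised, whatever care they go on to receive. A rule that takes people out of the study because they have deteriorated works against that, since the people removed are not a random subset. The trigger is somatic or psychiatric deterioration. Depression, anxiety and liver markers are outcomes in their own right, and drinking is plausibly related to all three.

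There are only two follow-up occasions. A participant withdrawn before week 13 would contribute baseline values alone, and one withdrawn later would lack week 52. A mixed model then fills the gap implicitly from participants who looked similar on the observed data, and the deterioration that led to removal may not be in those data. The decision is discretionary, and at least one person likely to be involved in it, the research nurse, knows the allocation. If poor outcomes leave one arm more often than the other, the estimated group difference shifts in favour of the arm that loses more of them.

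**Working it through.** **The yardstick.** The article plans on a standardised effect of 0.4 with 100 per arm, 80% power and two-sided 0.05. A two-sample t test needs 99.1 per arm, hence 100, and at 100 per arm the power is 80.4%. The stated figure reproduces, so biases below are read against 0.4 SD.

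**Inputs that the article does not give.** It states no rate of staff-initiated withdrawal, no difference between arms, and no figure for how much worse withdrawn participants do. All of these are assumptions below.

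**First-order formula.** Let w be the proportion withdrawn in an arm, and δ the amount by which the withdrawn do worse, in SD, than the model predicts for them. The arm mean is then too favourable by w × δ, and the bias in the group difference is (w_iCBT − w_TAU) × δ. With δ = 1:

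| Withdrawn, one arm vs the other | Bias (SD) | Share of 0.4 |
|---|---|---|
| 3% vs 1% | 0.02 × 1 = 0.02 | 5% |
| 10% vs 5% | 0.05 × 1 = 0.05 | 12.5% |
| 15% vs 5% | 0.10 × 1 = 0.10 | 25% |
| equal rates | 0 | 0% |

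With 260 / 2 = 130 per arm, 10% vs 5% means 13 against 6 or 7 people, and 3% vs 1% about 4 against 1.

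**Check by simulation under a different model.** 400,000 simulated participants per arm; baseline and follow-up correlated 0.5; a liability to complications correlated 0.5 with the part of the outcome that baseline does not explain; the highest-liability fraction of each arm removed; baseline-adjusted regression on those who remain. Estimated benefit of iCBT, in SD:

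| Withdrawn TAU / iCBT | True benefit 0.40 | True benefit 0 |
|---|---|---|
| none | 0.401 | −0.001 |
| 5% / 5% | 0.399 | 0.001 |
| 5% / 2% | 0.375 | −0.027 |
| 10% / 5% | 0.359 | −0.038 |
| 10% / 2% | 0.340 | −0.065 |
| 2% / 5% | 0.425 | 0.024 |
| 5% / 10% | 0.438 | 0.040 |

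The baseline adjustment does not remove the bias, because the removal depends on what happened after baseline. Equal rates leave the estimate essentially unchanged. More withdrawal in TAU shrinks the estimated benefit, and more in iCBT inflates it.

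**Scale.** At 100 per arm the standard error of an unadjusted difference is √(2/100) = 0.141 SD. A bias of 0.02 to 0.10 SD is 0.14 to 0.71 of that standard error.

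**The case against.** The strongest reply is that the rule is an ordinary, permissive safety provision, and that much of the harm has to be inferred.

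- *The article never says that follow-up stops.* This is correct. A reader might infer that week-13 and week-52 data are definitely lost. The text supports only that they may be. The reminders in the same section are described for participants generally, with no exception for the withdrawn, and the full protocol may say more. But leaving the study is what the sentence says, and nothing shown says that collection continues.
- *Unblinding is overstated if it is extended to GPs.* This is also correct. It is documented for the nurse alone, and the rule speaks of research personnel without naming her.
- *Intention-to-treat does not promise complete outcomes.* True: the article expects dropout, so this is not an outright contradiction. The rule does, however, let staff create missing data that could have been collected.
- *Failure of missing-at-random is not shown.* A reader might take it as certain, or suppose that most withdrawals precede any follow-up value. Neither is documented. The trigger is not drinking itself, the models adjust for baseline covariates, and 52 − 13 = 39 of the 52 weeks fall after the first follow-up.
- *Rates may be low.* Serious mental illness and need for specialist psychiatric or dependence care are exclusions, checked by telephone, and the article calls the risks minimal. This stands and argues for the lower end of the range.
- *These losses need not come on top of the 30% dropout.* The article does not define dropout, so that allowance may already include them.

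These points limit the size and certainty of the concern. They do not supply the missing statement about outcome collection.

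**Conclusion.** The point holds in a limited form. The withdrawal rule does not distinguish a change of care from the end of outcome collection. Read plainly, it may lose follow-up data for reasons related to the outcomes, in a trial where at least the research nurse knows the allocation. Such data are plausibly not missing at random, and neither the mixed model nor imputation of internal gaps can be relied on to repair that.

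The size is small to moderate: about 0.02 to 0.10 SD, or 5% to 25% of the planned 0.4, in either direction. That range rests on assumed withdrawal rates of 1% to 15%, differences between arms of 2 to 10 percentage points, and a shortfall of 1 SD; the simulated cases fall inside it. With equal rates there is essentially no bias in the group difference. The documents do not show that rates would differ, so this is an avoidable risk and not a demonstrated bias. It still deserves correction, because outcomes that were never collected cannot be recovered in the analysis.

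**What to change.** Leave the clinical decision and the referral as they are. Reconcile the withdrawal rule with the intention-to-treat statement by adding, in substance:

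- A withdrawal initiated by staff does not by itself end outcome collection, in either arm.
- Participants concerned are still invited to the week-13 and week-52 web assessments and, if willing, the blood tests, unless they themselves withdraw consent.
- Data so obtained enter the intention-to-treat analysis.
- The date, reason and arm of each staff-initiated withdrawal are recorded, so that rates can be compared between arms.

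The wording should concern outcome collection. Limiting the rule to stopping the study intervention would have no clear meaning in the TAU arm, where the treatment is ordinary GP care that the article says may continue.

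The cost is a short addition to the text plus a simple log. The web platform, nurse reminders and retrieval of blood results from patient files already exist. The downside is some further contact with referred participants. At the issue date of 5 June 2019, recruitment was to run to December 2019 and the study to December 2020, so the clarification could still protect follow-up data not yet due.
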